
### Endpoints for the interim analysis

2.10

An interim safety analysis will be performed at 30 days after study treatment of the third included patient, and the safety of continuing the trial will be evaluated by the Data and Safety Monitoring Committee. If two of the three patients develop a serious procedure-related AE (severe or fatal according to ASGE [American Society for Gastrointestinal Endoscopy] guidelines,^[14]^ or grade 4 or 5 according to CTCAE [Common Terminology Criteria for Adverse Events]), the study will be discontinued.

### Data collection

2.11

Baseline assessment will be performed during the screening period. Basic information including sex, age, date of birth, primary disease and date of first diagnosis, history, concomitant disease, and metal allergy to nickel-titanium will be recorded. To ensure feasibility and safety, complete blood counts, hepatic and renal function tests, and biochemical tests will be performed during the screening period.

CT will be performed during the screening period to determine the site of biliary obstruction and the tumor stage according to the TNM classification.^[15]^ Patients will undergo the above-mentioned blood tests on postprocedural days 1, 3, 7, 14, 21, 30, and 60 to evaluate the efficacy of the treatment, AEs, and stent dysfunction. CT will be performed postoperatively on days 0, 1, 14, 30, and 60 to evaluate the position of the stent, AEs, and stent dysfunction. Esophagogastroduodenoscopy will be performed postoperatively on days 14 and 60 to evaluate gastric mucosal damage by the stent. All patients will be followed until either death or 60 days after the treatment to record survival, concomitant medications, and concomitant therapy. The schedule for enrollment, interventions, and assessments is shown in Figure 2.

**Figure 2 F2:**
[figure not shown]
Standard protocol items (SPIRIT): schedule for data collection.

### Statistical analysis

2.12

#### Sample size calculation

2.12.1

In a meta-analysis on EUS-BD, the median rate of clinically effective improvement in 26 articles enrolling more than ten patients was 88.0%, and the median of 3 articles enrolling more than 100 patients was 89.5%.^[3]^ In addition, the median rate of clinically effective improvement in a randomized controlled trial was 87.5%.^[16]^ On the basis of these reports, we set the expected clinical response rate for this study to 88%. In the meta-analysis,^[3]^ the 5% point improvement in clinical efficacy of the 26 articles with more than ten cases was 72.5%. Therefore, we set the threshold for the clinically effective improvement rate to 73%. In this case, the minimum number of patients required to achieve a power of 80% or higher at the significance level of α-0.05 is 37 patients. We set the target number of patients to 40, assuming that a small number (about 10%) of patients will drop out of the study.

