### Study aims and design

2.2

This is a single-arm multicenter study across six tertiary centers in Japan that aims to evaluate the efficacy and safety of a system for endoscopic ultrasound-guided hepaticogastrostomy (HG01) in 40 patients with malignant biliary obstruction. The first three patients will be performed at the main institution, Wakayama Medical University. An interim analysis of safety will be performed after the procedure is completed on the first three patients, and the Data and Safety Monitoring Committee (DSMC) will evaluate the safety of the system and decide whether the trial can be continued afterwards. If the DSMC decides that the system is safe enough to continue the trial, the trial will be conducted in the remaining 37 patients at all participating institutions.

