#### Statistical analysis

2.12.2

In the effectiveness analysis for the population, the full analysis set (FAS) is the main analysis, and the per protocol analysis set (PPS) acts as a reference. In the safety analysis for the target population, all test examples will be analyzed. For the clinical success rate, a test of the mother ratio against the threshold clinical success rate of 0.73 will be performed for the FAS. The exact method will be used to calculate the *P*-value, and a one-sided test will be performed. If the *P*-value is below the significance level of α = 0.05, EUS-HGS using the HG01 system will be considered effective. For the rates of technical success, procedure-related AE, successful procedures using only the HG01 system, and stent patency at 30 days, the percentages and 95% Clopper–Pearson confidence intervals will be calculated. For the procedure time, the mean and 95% confidence interval will be calculated. For the overall survival time, the survival rate will be estimated using the Kaplan–Meier method, and the 95% confidence interval at each time point will be calculated using Greenwood's formula. In addition, a Kaplan–Meier plot will be used to draw the survival curve. For the distance of movement of the stent position at 1, 14, 30, and 60 days after treatment, the mean and 95% confidence interval will be calculated. We will also create transition charts for each case and for the mean values. Error bars representing standard error will be added to the mean trend chart. The number and percentage of AEs will be calculated for each grade of AEs. All analyses will be performed using R version 4.1.2 (The R Foundation for Statistical Computing, Vienna, Austria).

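### The stated 80% power at 37 patients does not hold for the planned exact one-sided test: at an 88% success rate, power is 56% to 72% with 36 to 40 patients analysed

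*Protocol article*

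**What the plan says.** All the inputs stand in two sections of the Protocol article.

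- **Sample size calculation (2.12.1).** For the expected rate, "we set the expected clinical response rate for this study to 88" per cent. For the null value, "we set the threshold for the clinically effective improvement rate to 73" per cent. The conclusion is that "the minimum number of patients required to achieve a power of 80% or higher at the significance level of α-0.05 is 37 patients". The target is then set at 40 to allow for about 10% dropout. This section names neither the test nor its sidedness.
- **Statistical analysis (2.12.2).** The primary test is made "against the threshold clinical success rate of 0.73 will be performed for the FAS". The exact method is to supply the P-value, and the sidedness is explicit: "a one-sided test will be performed". The success criterion applied to that result reads: "is below the significance level of α = 0.05, EUS-HGS using the HG01 system will be considered effective".

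The primary test is therefore fully specified: one proportion, null value 0.73, exact binomial, one-sided, 0.05, FAS.

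**The concern.** A minimum sample size for a stated power is a property of a particular test at particular rates. Both are printed, so the statement can be checked, and it fails.

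The trial has a single arm, and its conclusion on effectiveness rests on this one test. If power is lower than stated, a device that performs exactly as the investigators expect has a larger chance of not being declared effective. A reader who trusts the 80% would also give a non-significant result more weight than it deserves.

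**Working it through.** **Inputs.** From 2.12.1: null rate p0 = 0.73, expected rate p1 = 0.88, power at least 80%, stated minimum 37, target 40, dropout about 10%. From 2.12.2: exact binomial test, one-sided, 0.05, in the FAS.

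**Step 1: where 37 could come from.** No formula is given. Two routes lead to 37:

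- A Wald normal approximation at two-sided 0.05, with the variance taken at 0.88 only: n = (1.960 + 0.842)² × 0.88 × 0.12 / 0.15² = 36.8, rounded up to 37.
- The planned exact one-sided test at 0.05, but with an expected rate of 89.5%. That is the median which 2.12.1 quotes for the articles with more than 100 patients. Power is then 67.4% at 36 and 81.3% at 37, so 37 is the minimum.

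Other one-sided 0.05 formulas at 73% and 88% do not give 37: normal approximation with null and alternative variances 45, arcsine 42, Wald with the variance at 88% 30, null variance throughout 55.

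**Step 2: the planned test at the stated rates.** For each n, find the smallest k with P(X ≥ k | n, 0.73) ≤ 0.05. Power is P(X ≥ k | n, 0.88).

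| Patients in FAS | Successes needed | Exact type I error | P-value with one success fewer | Power at 88% |
|---|---|---|---|---|
| 36 | 32 | 1.88% | 0.0501 | 56.3% |
| 37 | 32 | 4.17% | 0.0939 | 72.0% |
| 38 | 33 | 3.45% | 0.0798 | 69.8% |
| 39 | 34 | 2.85% | 0.0676 | 67.6% |
| 40 | 35 | 2.35% | 0.0570 | 65.4% |
| 41 | 35 | 4.80% | 0.1010 | 78.4% |
| 46 | 39 | 4.55% | 0.0927 | 81.9% |

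The range 36 to 40 covers the plan's own expectations: 40 less 10% is 36, and 40 is no loss at all. The first n to reach 80% is 46. Power falls below 80% again at 48 to 50 and is at least 80% from 51 up to 74, the largest n checked.

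From 37 to 40, power falls as patients are added, because the required count rises by one with each extra patient. The attained type I error drops from 4.17% to 2.35% over the same steps.

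**Step 3: size of the gap.** Against 80%, the shortfall is 80 − 72.0 = 8.0 points at 37 and 80 − 65.4 = 14.6 points at 40. The chance of missing when the true rate is 88% runs from 100 − 72.0 = 28.0% (37 analysed) to 100 − 56.3 = 43.7% (36 analysed), and is 100 − 65.4 = 34.6% at 40. With 40 analysed, 34 successes (85%) give P = 0.057 and do not meet the criterion. Power of 80% at 40 would need a true rate of about 90.1%.

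**The case against.** The strongest reply is that 37 may be a correct calculation with a misprinted input. At 89.5% it is the exact one-sided minimum, so the test and alpha may have been right and the expected rate of 88% the slip. This stands as a possibility and makes the shortfall uncertain: at 89.5%, power is 81.3% at 37 and 76.1% at 40, a smaller gap than at 88%. It does not rescue the sentence, because 2.12.1 commits to 88%.

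A reader might infer from the Wald match that the sample size was computed for a different test at a different alpha. The document does not support that. It states no formula, and the second route gives the same number with the planned test.

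A reader might also take 65% as the power of the trial. That figure holds only if all 40 patients enter the FAS. The plan expects some loss, so the range over 36 to 40 is the fair statement.

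The rounding of the threshold deserves mention. The source figure in 2.12.1 is 72.5%. With 0.725 as the null value, the exact test has 80.2% power at 40, but still 72.0% at 37. Both sections fix 73%, so this does not make the statement true either.

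The 37 remaining patients in Study aims and design (2.2) are 40 minus the first three treated at the main institution. They are not the 37 of the power calculation.

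Finally, the exact test keeps type I error below 5% throughout, so a positive result is not in doubt. That is correct and limits the point to the power statement.

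**Conclusion.** The point holds in this form: 37 is not the minimum for 80% power with 88%, 73%, 0.05 and the exact one-sided test, and no FAS size from 36 to 40 reaches 80% at those rates. Power lies between 56.3% and 72.0%; the exact minimum is 46.

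This rests on the printed rates, on the test as described in 2.12.2, and on a FAS of 36 to 40 patients. It does not depend on how 37 was derived, which cannot be settled from the article. The consequence is a higher chance of a false-negative trial and a power figure that the design does not have, not a loss of type I error control.

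**What to change.** First establish which expected rate and method produced 37. Then, in 2.12.1, delete the claim that 37 is the minimum for 80% power and state the rule for the planned test, for example:

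> With 40 patients in the FAS, at least 35 successes are needed (exact one-sided type I error 2.4%, power 65% at a true rate of 88%). With 36 to 39 patients in the FAS, power is 56% to 72%.

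If 37 was derived from a different expected rate, state that rate, justify it, and give the exact power at 36 to 40 patients.

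The cost is a less favourable stated power. The test, alpha, threshold and enrolment target stay as they are, and no extra patients are needed. If the sponsor prefers to keep an 80% claim at 88%, wording alone will not do: the exact test then needs 46 patients analysed.

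### The target of 40 covers 7.5% dropout, not about 10%, and the planned exact test does not reach the stated 80% power whether dropouts are excluded or retained

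*Protocol article*

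**What the plan says.** Protocol article, section 2.12.1 (Sample size calculation):

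- Planning rate: "we set the expected clinical response rate for this study to 88" per cent.
- Null rate: "we set the threshold for the clinically effective improvement rate to 73" per cent.
- Minimum sample: "power of 80% or higher at the significance level of α-0.05 is 37 patients".
- Allowance for losses: "We set the target number of patients to 40, assuming that a small number (about 10%) of patients will drop out of the study".

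Section 2.12.2 (Statistical analysis) fixes the primary test. On populations: "the full analysis set (FAS) is the main analysis, and the per protocol analysis set (PPS) acts as a reference". The clinical success rate is tested against 0.73 in the FAS at α = 0.05. On the method: "The exact method will be used to calculate the" P-value, "and a one-sided test will be performed".

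The article does not define the FAS, does not define a dropout, and does not say whether a patient lost before the outcome is known is excluded or scored as a non-success.

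**The concern.** Two things do not fit.

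First, the three figures in 2.12.1 (minimum 37, target 40, about 10% lost) do not agree with each other.

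Second, raising 37 to 40 is a remedy for patients who leave the denominator. The primary test is run in the FAS. If the FAS retains treated patients who are lost, and scores them as non-successes, each loss lowers the success proportion and a few extra patients do not make up for it. The allowance therefore depends on a handling of dropouts that the article does not state.

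At stake is how a negative result is read. A trial believed to have 80% power with dropout already covered would suggest that the device fell short. If the power is nearer two thirds, or lower, the same result is much weaker evidence.

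**Working it through.** **Inputs.** p0 = 0.73, p1 = 0.88, minimum 37, target 40, dropout about 10% (all 2.12.1); exact one-sided test at α = 0.05 in the FAS (2.12.2).

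**1. The plan's own 37.** Of the formulas tried, one returns 37: the normal approximation with two-sided α = 0.05 and the variance taken at p1,
(1.960 + 0.842)² × 0.88 × 0.12 / 0.15² = 36.8, rounded up to 37.
This is not the planned test. With the one-sided exact binomial test, the first sample with at least 80% power is 46 (39 successes needed, attained α 0.0455, power 81.9%), and power stays at or above 80% only from 51.

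**2. The dropout allowance.**
- 40 × 0.90 = 36, below 37.
- (40 − 37)/40 = 3/40 = 7.5%, the largest loss that keeps 37.
- 37/0.90 = 41.1, so 42 enrolled would be needed to keep 37 after a 10% loss.

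**3. Power if dropouts are excluded.** For each n, take the smallest r with P(X ≥ r | n, 0.73) < 0.05; power is P(X ≥ r | n, 0.88).

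| Lost from 40 | n analysed | r needed | Attained α | Power |
|---|---|---|---|---|
| 0 | 40 | 35 | 0.0235 | 65.4% |
| 1 | 39 | 34 | 0.0285 | 67.6% |
| 2 | 38 | 33 | 0.0345 | 69.8% |
| 3 | 37 | 32 | 0.0417 | 72.0% |
| 4 | 36 | 32 | 0.0188 | 56.3% |

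Power rises slightly over the first three exclusions because the test is discrete. It drops at 36 because 32 successes are still required there.

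**4. Power if dropouts are retained and all count as failures.** The denominator stays at 40, so 35 successes are required and at most 5 failures are allowed. At 88% success, 40 × 0.12 = 4.8 failures are expected with no dropout at all.

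With a fixed number k of dropouts, power is P(X ≥ 35 | 40 − k, 0.88):
- k = 1: 49.0%
- k = 2: 31.6%
- k = 3: 16.3%
- k = 4: 5.9%

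With a dropout probability for each patient:
- 5%: 0.88 × 0.95 = 0.836, power 34.0%
- 10%: 0.88 × 0.90 = 0.792, power about 13%

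A modest enlargement does not repair this: with 10% counted as failures, power is 20.1% at 42 enrolled and 15.6% at 50.

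**The case against.** **The gap is rounding-level.** The text says about 10%, and the shortfall is one evaluable or two enrolled patients. This stands: alone, the 36 against 37 would be a footnote.

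**The FAS is not defined, so retention is an inference.** This also stands. A reader might infer from "the full analysis set (FAS) is the main analysis" that dropouts remain in the primary denominator as failures. The article does not say so. Under section 2.3 registration is complete before treatment, so the dropouts meant could be registered patients who are never treated and who might fall outside the FAS; the enlargement would then be coherent. An article may leave the FAS definition to the full protocol or analysis plan, and its absence is not the finding.

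**The 13% is a worst case.** It stands. Section 2.8 asks for T-Bil below half the pretreatment peak at two of days 3, 7, 14 and 21, so a patient can qualify by day 7. Follow-up runs to day 60 (2.11), and a loss after day 21 need not affect the primary endpoint. Multiplying 0.88 by 0.90 also assumes that dropouts would otherwise have succeeded at 88%; some may already belong to the 12% expected to fail.

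**Much of the shortfall belongs to the 37.** This stands too. Power is 65.4% at 40 with nobody lost, and 42 enrolled with no dropout gives only 76.6%. The excluded-dropout figures should not be charged to the dropout allowance alone.

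What the objections do not remove is that 40 does not cover a 10% loss from 37, and that no handling of dropouts examined here brings the planned test to 80%.

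**Conclusion.** The point holds in limited form. The statement that 40 allows for about 10% dropout from 37 is wrong by a small margin: 40 covers 3 losses, or 7.5%. The stated 80% power is not delivered by the planned exact one-sided test under either reading of the FAS:

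- no dropout: 65.4%
- 1 to 4 patients excluded: 67.6%, 69.8%, 72.0%, 56.3%
- dropouts retained, all as failures (worst-case scoring): about 34% at a 5% and 13% at a 10% dropout probability

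These figures assume true success of 88% in patients who are not lost, independent outcomes, and (in the last line) that every dropout counts as a failure. If some dropouts qualify before they are lost, or would have failed anyway, power lies above the last line.

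Two stronger readings are not supported. One is that the trial's power is 13%: that needs both retention in the FAS and failure of every dropout, and the article states neither. The other is that the design misses its stated sample size however dropouts are handled: if they are retained, the analysed number is 40, which exceeds 37. The 36 and the 13% belong to opposite assumptions and cannot both apply.

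**What to change.** In section 2.12.1:

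1. Withdraw the statement that 40 covers about 10% dropout, or replace it with 7.5% (3 patients).
2. Replace the 80% with the exact one-sided power at 40: about 65% with no dropout, 35 successes needed.
3. State which handling of dropouts the trial's FAS actually uses, and give the matching range. If excluded: 72.0% at 37 analysed and 56.3% at 36. If retained as non-successes: about 34% and 13% at 5% and 10% dropout, labelled worst case.

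Leave the primary endpoint in section 2.8 unchanged. In particular, do not add a rule that makes a patient without two qualifying T-Bil values a non-success: section 2.8 also lists a criterion based on a T-Bil decrease and duct diameter on day-14 CT, and such a rule would pass over it.

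The cost is wording and a less favourable stated power. No extra patients are needed. Correcting the allowance alone would not restore 80%, so items 1 and 2 should be made together.

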#### Statistical analysis

2.12.2

In the effectiveness analysis for the population, the full analysis set (FAS) is the main analysis, and the per protocol analysis set (PPS) acts as a reference. In the safety analysis for the target population, all test examples will be analyzed. For the clinical success rate, a test of the mother ratio against the threshold clinical success rate of 0.73 will be performed for the FAS. The exact method will be used to calculate the *P*-value, and a one-sided test will be performed. If the *P*-value is below the significance level of α = 0.05, EUS-HGS using the HG01 system will be considered effective. For the rates of technical success, procedure-related AE, successful procedures using only the HG01 system, and stent patency at 30 days, the percentages and 95% Clopper–Pearson confidence intervals will be calculated. For the procedure time, the mean and 95% confidence interval will be calculated. For the overall survival time, the survival rate will be estimated using the Kaplan–Meier method, and the 95% confidence interval at each time point will be calculated using Greenwood's formula. In addition, a Kaplan–Meier plot will be used to draw the survival curve. For the distance of movement of the stent position at 1, 14, 30, and 60 days after treatment, the mean and 95% confidence interval will be calculated. We will also create transition charts for each case and for the mean values. Error bars representing standard error will be added to the mean trend chart. The number and percentage of AEs will be calculated for each grade of AEs. All analyses will be performed using R version 4.1.2 (The R Foundation for Statistical Computing, Vienna, Austria).

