### Exclusion criteria

2.5

The following exclusion criteria will be applied.

(1)Impossible to perform endoscopy.(2)Total gastrectomy has already been performed.(3)Left hepatectomy has already been performed.(4)Bismuth classification for hilar biliary carcinoma: Type IIIb or Type IV.(5)Liver cirrhosis.(6)Ascites around the liver on CT.(7)With percutaneous trans-hepatic biliary drainage (PTBD) tube at time of obtaining informed consent.(8)Planned insertion of a metal stent in the upper gastrointestinal tract within 7 days before treatment.(9)Performance status 4.(10)Other severe diseases of the heart, lung, kidney, and/or liver of ASA 4 or higher.(11)Poor general condition and estimated prognosis of less than 2 months.(12)Hemorrhagic diathesis including fatal aneurisms or severe coagulation disorder.(13)Participation in other clinical trials (except in a non-intervention arm).(14)Women who may possibly be pregnant or who want to be pregnant.(15)Metal allergy to nickel-titanium.(16)Known allergy to iodine contrast agents.(17)Patients whom the investigators otherwise decide are inappropriate to participate in the trial.

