### Secondary endpoints

2.9

The secondary endpoints are as follows:

(1)Technical success rateTechnical success is defined as the stent being positioned between the stomach and intrahepatic bile duct, as seen on CT performed 1 day after treatment.(2)Procedure-related adverse event (AE) rateProcedure-related AEs are defined as AEs judged to be “related,” “possibly related,” or “might be related” to the procedure. Procedure-related AEs will be divided into early AEs occurring within 14 days after treatment and late AEs occurring from 15 to 60 days after treatment. Early AEs may include postprocedural pancreatitis, cholangitis, stent migration, stent deviation, gastric ulcer associated with mechanical irritation of the stent, bleeding, gastrointestinal injury, and procedure-related deaths. Late AEs may include stent migration, stent deviation, stent occlusion, and gastric ulcer associated with mechanical irritation from the stent.(3)Procedure timeProcedure time is defined as the time from the puncture of the bile duct to stent placement.(4)Procedure success rate using only the HG01 systemProcedure success using only the HG01 system is defined as successful insertion of the stent into the left intrahepatic bile duct using only the HG01 system.(5)Stent patency rate at 30 and 60 days after treatmentThe stent patency rates are defined as the percentage of patients who do not experience stent dysfunction from the date of stent insertion to 30 and 60 days after treatment.Stent dysfunction is defined as follows.(1)A T-Bil level of ≥3.0 mg/dL when the lowest T-Bil level measured after treatment is <1.5 mg/dL.(2)A T-Bil level more than 2.0 times the lowest level when the lowest T-Bil level measured after treatment is more than 1.5 mg/dL.(6)Re-intervention success rate and re-intervention methodRe-intervention success is defined as the placement of a new drainage tube and improvement in the T-Bil level to below 50% of the highest pretreatment level within 21 days after re-intervention.The following re-intervention methods can be selected.(1)Treatment from the stent(2)Other EUS-guided biliary drainage(3)Trans-papillary biliary drainage(4)Percutaneous transhepatic biliary drainage(5)Surgical cholangiojejunostomy(7)Survival rate at 60 days after treatment(8)Distance of movement of the stent position at 1, 14, 30, and 60 days after treatmentThe length of the stent inside the stomach on the abdominal CT at day 0 after treatment will be compared with the length of the stent inside the stomach on days 1, 14, 30, and 60 after treatment, to evaluate the distance of movement of the stent from its placement position.

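### Minor: the Greenwood intervals planned for survival in 40 patients have no stated scale, can be too narrow when survival is high, and have zero width before the first death

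*Protocol article*

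**What the plan says.** The secondary endpoints (2.9) include "Survival rate at 60 days after treatment". No threshold or test is attached to it.

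For overall survival, Statistical analysis (2.12.2) states that "the survival rate will be estimated using the Kaplan–Meier method", "and the 95% confidence interval at each time point will be calculated using" Greenwood's formula. It names no scale (plain, log or log-log) and gives no rule for times when the estimate is 100%.

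The same paragraph treats four other rates differently. For technical success, procedure-related AEs, success with the HG01 system alone and 30-day patency, "the percentages and 95% Clopper–Pearson confidence intervals will be calculated".

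On follow-up, Data collection (2.11) says "All patients will be followed until either death or 60 days after the treatment to record survival". Sample size calculation (2.12.1) says "We set the target number of patients to 40", "assuming that a small number (about 10%) of patients will drop out of the study". Exclusion criterion 11 (2.5) reads "Poor general condition and estimated prognosis of less than 2 months". The article gives no expected figure for 60-day survival.

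**The concern.** If every patient is followed to death or day 60, nobody is censored before day 60. Greenwood's variance is then the ordinary binomial variance, and an interval built directly on it is the Wald interval. That interval is known to be too narrow for small samples and proportions near 100%. An interval is promised at each time point, and every survival curve starts at 100%, so at least the early part of the curve lies in that region.

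Until the first death the variance is zero and the printed interval is a single point. For a new device in 40 patients, that shows a certainty the data cannot give. An exact interval is already in use in the same paragraph.

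**Working it through.** **Inputs.** n = 40 (2.12.1). Two-sided 95% level, z = 1.96, Greenwood variance (2.12.2). Planned follow-up to death or day 60 (2.11), with about 10% dropout assumed (2.12.1). True survival S is not given, so a range is shown. The article states no survival rate or interval width, so there is no figure of its own to reproduce.

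**Step 1: variance.** Greenwood's formula is Var(Ŝ) = Ŝ² Σ dᵢ / [nᵢ(nᵢ − dᵢ)]. Without censoring it reduces to Ŝ(1 − Ŝ)/n.

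**Step 2: one worked case, 36 of 40 alive.** Ŝ = 0.90 and se = √(0.90 × 0.10 / 40) = 0.0474.
- Plain: 0.90 ± 1.96 × 0.0474 = 0.807 to 0.993.
- Log: 0.90 × exp(±1.96 × 0.0474 / 0.90) = 0.812 to 0.998.
- Log-log: Ŝ raised to the power exp(±1.96 × se / (Ŝ|ln Ŝ|)) = 0.755 to 0.961.
- Clopper–Pearson: 0.763 to 0.972.

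**Step 3: the edge.**
- 39 of 40 alive: plain 0.927 to 1.023, log 0.928 to 1.025 (both before truncation at 1), log-log 0.835 to 0.996, Clopper–Pearson 0.868 to 0.999.
- 40 of 40 alive: the variance is 0, so plain, log and log-log all give 1.000 to 1.000. The Clopper–Pearson lower limit is 0.025^(1/40) = 0.912.

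**Step 4: coverage.** For each S, the Binomial(40, S) probabilities were summed over the outcomes whose interval contains S.

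| True S | Plain | Log | Log-log | Clopper–Pearson | Chance of no death, S⁴⁰ |
|---|---|---|---|---|---|
| 0.70 | 0.930 | 0.938 | 0.959 | 0.961 | 0.000 |
| 0.75 | 0.945 | 0.952 | 0.958 | 0.972 | 0.000 |
| 0.80 | 0.905 | 0.916 | 0.949 | 0.973 | 0.000 |
| 0.85 | 0.939 | 0.947 | 0.969 | 0.976 | 0.002 |
| 0.90 | 0.914 | 0.914 | 0.943 | 0.970 | 0.015 |
| 0.92 | 0.837 | 0.837 | 0.927 | 0.987 | 0.036 |
| 0.95 | 0.868 | 0.871 | 0.823 | 0.986 | 0.129 |
| 0.98 | 0.553 | 0.554 | 0.509 | 0.992 | 0.446 |

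Over a fine grid from 0.70 to 0.95, mean coverage is 0.917 (plain), 0.916 (log), 0.948 (log-log) and 0.972 (Clopper–Pearson). The lowest values on that grid are 0.796, 0.797, 0.823 and 0.952. Coverage moves in a sawtooth, so single values should not be read as a trend.

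**Step 5: with loss to follow-up.** A Kaplan–Meier simulation (20,000 runs per setting) with 10% lost by day 60 gave similar coverage for plain/log/log-log: 0.927/0.916/0.956 at S = 0.80, 0.897/0.901/0.950 at 0.90 and 0.856/0.856/0.820 at 0.95.

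**Step 6: does a rule for 100% repair log-log?** If 40 of 40 alive is reported as 0.912 to 1.000, that outcome counts as covered whenever S is at least 0.912. Without censoring, coverage rises to 0.823 + 0.129 = 0.952 at S = 0.95 and to 0.509 + 0.446 = 0.955 at S = 0.98.

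**The case against.** Kaplan–Meier with Greenwood's variance is a standard choice, and zero width before the first event is a known property of every such curve. The scale is commonly left to the analysis plan, which is not shown. The log-log scale, which the wording allows, covers about 93% to 97% for true survival of 70% to 92.5% and cannot exceed 100%. The method also handles censoring, which a simple Clopper–Pearson interval does not. No decision depends on the survival interval: the safety rates are AE rates, which get exact intervals, and the interim rule counts serious AEs.

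Most of this stands, and it rules out several stronger readings that a reader might infer:
- **That Greenwood intervals here generally cover well below 95%, or must exceed 100%.** This depends on a scale that the article does not fix.
- **That survival will be high.** Exclusion criterion 11 rests on an estimated prognosis in patients with unresectable cancer. It makes high survival plausible but gives no figure.
- **That follow-up is complete.** It is planned, but about 10% dropout is assumed.
- **That every other rate gets Clopper–Pearson.** It is named for four rates. It is not named for 60-day patency or re-intervention success, and the primary endpoint is given an exact test.
- **That Clopper–Pearson always covers at least 97%.** It covers 95.3% at S = 0.91.

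The objection does not remove the zero-width interval, which no choice of scale cures, or the shortfall on all three scales at about 95% survival and above. An interval at each time point is a stated commitment, not a detail left open.

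**Conclusion.** The point holds as a minor one. With 40 patients and no censoring, plain or log-scale Greenwood intervals cover about 92% on average for true survival of 70% to 95%, with lows near 80%. Log-log intervals average about 95% over that range but drop to 82% at 95% survival. Before the first death the interval is 100% to 100% on every scale, where the exact one for 40 of 40 alive is 91.2% to 100%.

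The coverage figures rest on an assumed survival range and, apart from the simulation, on no loss before day 60. The zero-width result needs neither assumption. The endpoint is secondary and descriptive, so the effect is on how honest the error bars are, not on any trial conclusion.

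**What to change.** Add a short rule to 2.12.2:
- If no patient is lost before day 60, report 60-day survival as a percentage with the 95% Clopper–Pearson interval already named for technical success, AE rate, HG01-only success and 30-day patency.
- If any patient is censored earlier, use the Kaplan–Meier estimate with a log-log Greenwood interval.
- At any time before the first death, replace the zero-width interval with the exact binomial lower bound based on the number still at risk. With 40 at risk this is 91.2%. With 36 at risk (10% of 40 lost) it is 0.025^(1/36) = 90.3%.
- Keep Kaplan–Meier for the curve.

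The cost is two or three sentences and slightly wider, somewhat conservative intervals. No extra data are needed, and the sample size and primary analysis are unaffected.
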